| Study Type:           | A prospective, single-center, randomized, double-blind clinical trial                                                                                                                                                                                                                                                                                                                                                                                                                                                        |
| Corresponding Author: | [name], Department of Anesthesiology, The Affiliated Hospital of Xuzhou Medical University, Xuzhou, China. NMPA Key Laboratory for Research and Evaluation of Narcotic and Psychotropic Drugs & Jiangsu Province Key Laboratory of Anesthesiology & Jiangsu Province Key Laboratory of Anesthesia and Analgesia Application Technology, Xuzhou Medical University, Xuzhou 221004, Jiangsu, China.

[name], Department of Anesthesiology & Clinical Research Center for Anesthesia and Perioperative Medicine & Key |

|                            |                                                                                                                                                                                                                                                                                                                                                           |
|----------------------------|-----------------------------------------------------------------------------------------------------------------------------------------------------------------------------------------------------------------------------------------------------------------------------------------------------------------------------------------------------------|
|                            | Laboratory of Anesthesia and Analgesia Application Technology, Huzhou Central Hospital, The Fifth School of Clinical Medicine of Zhejiang Chinese Medical University    Huzhou Central Hospital, The Affiliated Central Hospital Huzhou University    Affiliated Huzhou Hospital, Zhejiang University School of Medicine, Huzhou 313003, Zhejiang, China. |
| Study Centers:      | The Affiliated Hospital of Xuzhou Medical University                                                                                                                                                                                                                                                                                                      |
| Ethics              | Approved by the Medical Ethics Committee of the Affiliated Hospital of Xuzhou Medical University (XYFY2024-KL053-02)                                                                                                                                                                                                                                      |
| Trial Registration: | www.chictr.org.cn Identifiers: ChiCTR2400082716                                                                                                                                                                                                                                                                                                           |

12

## 13 **1. Study Objectives**

14 Postpartum uterine contraction pain is a severe, episodic lower abdominal  
15 discomfort experienced by women during the early postpartum period as a  
16 result of uterine contraction. Transcutaneous auricular vagus nerve stimulation  
17 (taVNS) has demonstrated promising efficacy in the management of both  
18 acute and chronic pain conditions.

19 The objective of this study is to evaluate the efficacy of taVNS in  
20 alleviating postpartum uterine contraction pain in elective cesarean section  
21 women under combined spinal-epidural anesthesia.

22

## 23 **2. Background**

Cesarean delivery is a critical, life-saving surgical procedure utilized in situations such as prolonged labor, obstructed labor, fetal distress, or abnormal fetal positioning. In addition to the common short-term and long-term risks associated with surgical procedures, women undergoing cesarean delivery also experience postpartum uterine contraction pain comparable to that experienced by women who deliver vaginally. Postpartum uterine contraction pain typically emerges within 1 to 2 days following delivery and is characterized by intermittent and intense lower abdominal discomfort. The frequent and intense nature of uterine contraction is closely related to perioperative anxiety, depression, and sleep disturbances, which can adversely affect the quality of postpartum recovery and pose significant risks to the mother's physical and psychological well-being. Therefore, it is imperative to address and mitigate the pain associated with uterine contraction following cesarean delivery surgery.

Currently, the most commonly employed analgesic methods include epidural analgesia and intravenous administration of analgesics. While all of these methods are effective, they all have different side effects, including drowsiness, nausea, vomiting, itching, constipation, and respiratory depression. Moreover, these medications may impact the breastfed neonate, thereby imposing an additional psychological burden on the mother during lactation.

Transcutaneous auricular vagus nerve stimulation (taVNS) is a noninvasive neuromodulation technique that delivers low-intensity electrical current through electrodes to stimulate the auricular branch of the vagus nerve. taVNS exerts analgesic effects by modulating the vagus nerve system and its projections to pain-specific brain nuclei, and has also been shown to alleviate anxiety and depression in patients. However, there is limited research on the impact of taVNS on postpartum uterine contraction pain. Therefore, this study aims to investigate the analgesic effect of taVNS on postpartum uterine contraction pain and to explore its potential in promoting postpartum recovery in women under combined spinal-epidural anesthesia for elective cesarean delivery.

### **3. Methods**

This randomized, double-blind, controlled trial is conducted at the Department of Anesthesiology and Obstetrics of the Affiliated Hospital of Xuzhou Medical University. The study protocol received approval from the Ethics Committee of the Affiliated Hospital of Xuzhou Medical University (approval number: XYFY2024-KL053-02) and registered with the China Clinical Trial Registry on April 6, 2024 (ChiCTR2400082716). This report follows the Consolidated Standards of Reporting Trials (CONSORT) guidelines for randomized studies.

#### **3.1 Recruiting Methods and Consent Procedure**

The day prior to surgery, potential participants are identified from the women

scheduled for elective cesarean section. All potential participants who meet the inclusion criteria as defined by the chief anesthesiologist and designated personnel are invited to participate in the study. During the screening phase, participants or their legal surrogates are provided with the informed consent form, allowing them the opportunity to thoroughly review the document, ask any questions, and seek clarification on any aspect of the study. Prior to signing the consent form, the researchers address further inquiries from the participants. Once the consent form is signed, the participant receive a copy of the signed and dated form, with another copy placed in the medical records at the Affiliated Hospital of Xuzhou Medical University.

### **3.2 Inclusion Criteria and Exclusion Criteria**

Inclusion criteria include women with a singleton pregnancy at 37–42 weeks of gestation; aged 18 years or older; classified as American Society of Anesthesiologists (ASA) physical status classification of II or III; scheduled to undergo a cesarean delivery via a lower segment transverse incision under combined spinal-epidural anesthesia. Exclusion criteria include refusal to sign the informed consent form, a history of neurological or psychiatric disorders, cognitive impairment or communication difficulties, auricular dermatitis, substance abuse, or an inability to use patient-controlled intravenous analgesia. Participants may withdraw from the study for reasons such as voluntary withdrawal, poor adherence, protocol deviations, or failure to complete follow-up.

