### **3.5 Outcome measures**

#### **3.5.1 Primary outcome**

The primary outcome is the incidence of moderate to severe uterine contraction pain on the third postoperative day. Pain intensity is evaluated using the Visual Analogue Scale (VAS). The VAS is a well-established tool for evaluating pain, consisting of a 100 mm line where one end represents "no pain" and the other end signifies "the worst pain imaginable" or "the most extreme pain possible". Participants are asked to mark the point on the line that best corresponded to their perceived pain intensity. In this study, uterine contraction pain is classified as moderate to severe if the VAS score is 4 or higher.

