### **3.7 Sample Size Calculation**

Based on our preliminary observation, the incidence of moderate to severe uterine contraction pain on the third postoperative day following a lower-segment transverse cesarean delivery is approximately 35% (7 out of 20 patients). Considering that the number needed to treat for a moderate treatment effect for neuropathic pain is 4-10, we set the NNT at 5 and the absolute risk reduction (ARR) between the control and the intervention groups as 0.2. Given the ARR value of 0.2, we hypothesized that after three sessions of the active taVNS, the incidence of moderate to severe uterine contraction pain on the third postoperative day would be reduced to 15%. The sample size calculation for comparing two proportions was performed using the Z-Test with Unpooled Variance. The power calculation employed the Normal Approximation method, with a Two-Sided Alternative Hypothesis specified to assess statistical significance of the proportional difference. The

test type was defined as Unpooled Z-Test to accommodate potential between-group variance heterogeneity. A strategy of equal sample allocation ( $N_1 = N_2$ ) was adopted, with input parameters specified as proportions. With a statistical power of 0.80 and  $\alpha = 0.05$ , we calculated that a sample size of 70 patients per group was required using PASS version 15.0 (NCSS). Assuming a 10% loss to follow-up, we planned to recruit 78 participants per group.

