### **3.8 Intervention with taVNS**

On the day of delivery, the first postpartum day, and the second postpartum day, the intervention group received three sessions of active taVNS in total, and the control group received three sessions of sham taVNS in total. Electrical stimulation is applied through electrodes placed on the left concha of the ear (tVNS501; Changzhou Ruishen'an Medical Devices Co., Ltd.). In the active taVNS group, participants receive taVNS (pulse width: 200  $\mu$ s; frequency: 20 Hz) for 30 minutes, with the current increasing for 30 seconds until the participant reports a tingling sensation, then decreasing to a level slightly below this threshold for 30 minutes. In the sham taVNS group, electrodes are positioned similarly, with the current increasing for 30 seconds until the participant reported a tingling sensation, then decreasing to a level slightly below this threshold, after which the device remained off for the following 30 minutes to simulate the sham state. Throughout the intervention, researchers closely monitor participants for any adverse effects and stop the

stimulation immediately if intolerable side effects are observed.

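### Section 3.2 makes poor adherence and protocol deviations reasons to leave the study, which permits avoidable loss of third-day pain outcomes and may bias the primary comparison in either direction

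*Protocol*

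**What the plan says.** Protocol section 3.2, after the eligibility criteria: "Participants may withdraw from the study for reasons such as voluntary withdrawal, poor adherence, protocol deviations, or failure to complete follow-up". The sentence concerns leaving the study. It does not distinguish this from stopping the sessions, and it does not mention the analysis.

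The endpoint is in section 3.5.1: "The primary outcome is the incidence of moderate to severe uterine contraction pain on the third postoperative day". Section 3.4 places that assessment at T7, the morning of the third postoperative day, after all three sessions. Section 3.3 keeps the allocation concealed until the first session in the ward.

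Section 3.6 analyses the incidence of moderate to severe pain by a logit GEE with group, time and their interaction, clustered on participant, with an independent correlation structure. Section 3.7 covers attrition in one sentence: "Assuming a 10% loss to follow-up, we planned to recruit 78 participants per group". Section 3.8 tells researchers to stop "stimulation immediately if intolerable side effects are observed".

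**The concern.** Two of the four listed reasons, voluntary withdrawal and failure to complete follow-up, describe data that are lost whatever the plan says. The other two do not. A woman who skips the second session, or whose care departs from the protocol, can still mark a pain scale on the third day. If she is taken out of the study, the plan itself creates the missing value.

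This belongs in the protocol because site staff follow the protocol in deciding whom to keep following. An SAP can define an intention-to-treat set or an imputation method, but it cannot recover a T7 score that was never collected.

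The loss need not be neutral. Allocation is opened at the first session, so poor adherence to sessions comes after randomisation and can depend on what was delivered and how the woman felt. After the ramp, only the active device stays on for 30 minutes, so a difference between arms in tolerance or adherence is possible. If the women lost differ in pain from those kept, and differ more in one arm than in the other, the T7 comparison is no longer the randomised one.

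**Working it through.** **Plan's own figures.** Inputs from section 3.7: control 35%, active 15%, unpooled Z-test, two-sided alpha 0.05, power 0.80.

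n = (1.95996 + 0.84162)² × (0.35×0.65 + 0.15×0.85) / 0.20² = 7.849 × 0.355 / 0.04 = 69.66, rounded up to 70. With 10% loss, 70/0.90 = 77.8, so 78. Both stated figures reproduce. Power is 80.2% with 70 per group and 84.2% if all 78 are kept.

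**What a withdrawn woman contributes.** Section 3.6 compares groups at each time point, so I take time as a factor. With group, time, their interaction and independent working correlation, the fitted T7 values are the observed T7 proportions. Earlier scores from a woman with no T7 value do not enter the T7 contrast.

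**Selective loss, active arm only, no true effect.** Assumptions, not document figures: a fraction w of the active arm is withdrawn, and a fraction q of those women would have had moderate to severe pain. The true rate is 35% in both arms, with 78 randomised per arm and no loss from sham.

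Rate among active women kept = (0.35 − w×q)/(1 − w).

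Rejection probability = Φ(d − 1.96) + Φ(−d − 1.96), where d is the apparent difference divided by its unpooled standard error, with 78(1 − w) active and 78 sham women.

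Worked case, w = 0.10 and q = 0.80: the rate kept is (0.35 − 0.08)/0.90 = 0.300. The standard error is √(0.35×0.65/78 + 0.30×0.70/70.2) = 0.0769, so d = 0.05/0.0769 = 0.650 and the rejection probability is 10.0%.

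| w | q | Active rate observed | Apparent reduction (points) | Type I error |
|---|---|---|---|---|
| 5% | 35% | 35.0% | 0 | 5.0% |
| 5% | 100% | 31.6% | 3.4 | 7.3% |
| 10% | 35% | 35.0% | 0 | 5.0% |
| 10% | 60% | 32.2% | 2.8 | 6.5% |
| 10% | 80% | 30.0% | 5.0 | 10.0% |
| 10% | 100% | 27.8% | 7.2 | 15.8% |

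If sham also loses 10%, but at random, the last three errors become 6.4%, 9.7% and 15.2%. The selectivity matters far more than the imbalance in numbers.

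**Selective loss in the sham arm.** The same formula with the arms exchanged gives apparent differences of 2.8 to 7.2 points against active at w = 10%. Under the planned effect, suppose 10% of sham women are lost and 80% of them have pain. The observed sham rate is then (0.35 − 0.08)/0.90 = 30%. With 70 per arm kept and active at 15%, the standard error is √(0.30×0.70/70 + 0.15×0.85/70) = 0.0694 and d = 0.15/0.0694 = 2.16. Power is Φ(2.16 − 1.96), about 58%, against the planned 80%.

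**The case against.** The best defence is that section 3.2 says only that participants may withdraw. The wording is permissive, and failure to complete follow-up in the same list suggests a loose catalogue of reasons for non-completion. A reader might infer that these women are excluded from the analysis, or that their T7 score is never taken; the protocol says neither. Analysis sets and missing-data handling may be in the SAP, which is not at hand, so the absence of an intention-to-treat statement is not part of this point. What remains is the conduct rule: it makes adherence and deviations grounds for leaving, and nothing in the protocol says that such women continue to be assessed.

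A reader might also infer that the bias runs towards active taVNS. The documents do not support that. It would require withdrawn active women to have more pain than those kept, by a larger margin than in sham. Several things weaken that route:
- Participants, data collectors and other healthcare staff are blinded (section 3.3).
- The active current is set slightly below the tingling threshold (section 3.8), and adverse events are described as typically mild (section 3.5.3).
- Section 3.8 stops the stimulation for intolerable effects; it does not say that the woman leaves the study.
- Deviations during surgery or anaesthesia happen before allocation is opened, so treatment cannot cause them.

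These points make strongly selective loss less likely, but they do not exclude it. Blinding does not prevent a difference caused by the stimulation itself.

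Finally, the larger error rates rest on assumed extremes. At 5% withdrawn the error reaches 7.3% at most, and if withdrawn women resemble the rest there is no bias.

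**Conclusion.** The point holds as a defect in a conduct rule. Section 3.2 permits avoidable loss of the primary outcome after randomisation, and under the stated GEE such a woman drops out of the T7 contrast unless her score is still collected or imputed. The possible consequence ranges from none to material: with 10% selective loss in one arm, up to 7.2 points of apparent difference either way, and a type I error of up to 15.8% under the null. The 10% allowance in section 3.7 replaces lost numbers; it does not correct for selective loss.

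The size rests on assumed withdrawal shares and pain rates, on time being a factor in the model, and on no T7 score being collected or imputed for withdrawn women. Neither a fixed direction nor actual exclusion from the analysis is established. This is a should-fix, with medium confidence.

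**What to change.** Reword section 3.2 to separate ending the sessions from ending study participation. Missed or stopped sessions and protocol deviations should be recorded but should not end participation. Outcomes, at least T7 contraction pain, should continue to be collected from every randomised woman unless she withdraws consent or cannot be reached. These women should be analysed in the group to which they were randomised, with any per-protocol analysis as sensitivity only. The instruction in section 3.8 on stopping stimulation is not affected.

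The cost is a wording change and one pain score from each woman who would otherwise have left. The protocol does not say whether every woman is still in hospital on the third postoperative morning, so a few scores may need a follow-up contact. The sample size stays at 78 per group. The one statistical downside is that non-adherence may slightly dilute the effect estimate.

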### **3.3 Randomization and Blinding**

Participants are randomly assigned in a 1:1 ratio to either the active taVNS group or the sham taVNS group based on a computer-generated random number sequence. The allocation information is concealed in opaque envelopes and remains concealed until participants are ready to initiate the first intervention in the ward. All personnel involved in data collection, processing, and analysis, as well as other healthcare staff and participants, are blinded to the group assignments. Blinding will be disclosed after statistical analysis of the trial results.

### **3.4 Follow-up Plan**

On the day before the parturient's surgery (T0), researchers will collect baseline data, and assess sleep at T0 on the morning of the surgery. On the day of the surgery, before the first intervention (T1), blinded researchers will evaluate the peak uterine contraction pain and incision pain. After the first intervention (T2), depression and anxiety will be assessed, followed by re-evaluation of peak uterine contraction pain and incision pain during this period. Sleep at T2 will be assessed on the morning of the first postoperative day. Before the second intervention (T3), peak uterine contraction pain and incision pain will be evaluated. After the second intervention (T4), depression, anxiety, postpartum recovery quality, and peak uterine contraction pain and incision pain during this period will be assessed. Sleep at T4 will be evaluated on the morning of the second postoperative day. Before the third intervention

(T5), peak uterine contraction pain and incision pain will be evaluated. After the third intervention (T6), depression, anxiety, postpartum recovery quality, and peak uterine contraction pain and incision pain during this period will be assessed. On the morning of the third postoperative day (T7), sleep at T6 will be evaluated, along with peak uterine contraction pain, incision pain, depression, anxiety, and postpartum recovery quality. At 1 month postpartum (T8), the telephone follow-up will assess the parturient's depressive and anxiety status.

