#### **3.5.2 Secondary outcomes**

1) Peak uterine contraction pain scores during the three days postoperatively (assessed by the VAS). The contraction pain scores are measured before the

first intervention (T1), after the first intervention (T2), before the second intervention (T3), after the second intervention (T4), before the third intervention (T5), after the third intervention (T6), and the third postoperative day (T7).

2) Incision pain scores at T1-T7 (assessed by the VAS).

3) Maternal anxiety scores at T2, T4, T6, T7 and the first month postpartum [T8] (assessed by the Pregnancy-Related Anxiety Questionnaire-Revised 2 [PRAQ-R2], comprising 10 items, each rated on a 5-point scale [1-5], with higher scores indicative of increased pregnancy-related anxiety).

4) Maternal depression scores at T2, T4, T6, T7, and T8 (assessed by the Edinburgh Postnatal Depression Scale [EPDS], including 10 items, scored on a 4-point scale [0-3], with higher scores denote more severe depressive symptoms).

5) Sleep quality at T2, T4 and T6 (assessed by the Leeds Sleep Evaluation Questionnaire [LSEQ], with higher scores indicating better sleep quality).

6) Quality of postpartum recovery at T4, T6 and T7 (assessed by the 11-item Obstetric Quality Recovery Scale [ObsQoR-11], with a total score range of 0-110).

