### **3.6 Statistical Analysis**

Descriptive statistics will include the Chi-squared test or Fisher exact test for categorical variables expressed as frequency. Assessment for normal distribution will be performed with the Shapiro–Wilk test. Normally distributed data will be presented as mean and standard deviation (SD) and compared by the independent sample t-test. Non-normally distributed data will be presented as median and interquartile range (IQR) and compared by the Mann-Whitney U test.

For data collected at multiple time points, we will adopt the Generalized Estimating Equations (GEE). First, we will test the interaction between treatment and time. If this interaction is significant, we will test the between-group differences at each time point and use the Bonferroni test to adjust for multiple comparisons. Otherwise, we will next test the main effect of treatment, and the Bonferroni correction will not be performed for the treatment effects at each time point. For the comparison of the incidence rate of moderate to severe postpartum contraction pain, the GEE model will include the following settings: covariates: intervention group, time, intervention  $\times$  time interaction; link function: logit function; group variable: participant; intraclass

correlation structure: independent. The GEE models for contraction pain score, incision pain score, depression score, anxiety score, sleep score, and recovery quality score will include the following settings: covariates: intervention group, time, intervention  $\times$  time interaction; link function: identity link; group variable: participant; intraclass correlation structure: independent. Data will be analyzed using SPSS version 27.0 (IBM Corp., Chicago, ILUSA) and GraphPad Prism V.9 (GraphPad Software, San Diego, CAUSA), with  $P < .05$  considered statistically significant.

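### No pre-treatment depression or anxiety score is specified, and the models for these two secondary outcomes adjust for none, so they are less precise than they could be

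*Protocol*

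**What the plan says.** Protocol section 3.4 describes two contacts before the first session. At T0, the day before surgery, "researchers will collect baseline data, and assess sleep at T0 on the morning of the surgery". The baseline data are not itemised. At T1, on the day of surgery, "before the first intervention (T1), blinded researchers will evaluate the peak uterine contraction pain and incision pain". Neither contact names depression or anxiety. They first appear after session 1: "After the first intervention (T2), depression and anxiety will be assessed".

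Section 3.5.2 agrees. It lists "Maternal depression scores at T2, T4, T6, T7, and T8", and gives the anxiety score the same five time points. Sleep is listed as "Sleep quality at T2, T4 and T6", although section 3.4 also measures it at T0.

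Section 3.6 sets out one specification for all the score outcomes: "The GEE models for contraction pain score, incision pain score, depression score, anxiety score, sleep score, and recovery quality score will include the following settings". The settings that follow are group, time and group-by-time as covariates, an identity link, and an independent working correlation. No baseline score enters any of these models.

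**The concern.** The T2 score is taken after the first stimulation session, so it cannot serve as a baseline. Contraction and incision pain have a pre-treatment value at T1 and sleep has one at T0. Depression and anxiety have none by name. Differences between women that were present before treatment and persist afterwards therefore stay in the error term for these two outcomes, and a reader of the results cannot see whether the arms were alike on them at entry.

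This cannot be left to a later analysis plan, because no analysis can recover a score that was not collected. The two outcomes also matter to the trial's argument. Section 2 cites anxiety and depression as part of the rationale, and they are the only outcomes followed to one month (T8).

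**Working it through.** **The plan's own figure.** The only calculated figure is the sample size for the primary outcome (section 3.7), with inputs 35% against 15%, two-sided alpha 0.05, power 0.80 and an unpooled Z-test:

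n = (1.960 + 0.842)² × (0.35 × 0.65 + 0.15 × 0.85) / 0.20² = 7.849 × 0.355 / 0.04 = 69.66, rounded up to 70.

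For 10% loss, 70 / 0.90 = 77.8, rounded up to 78. Both figures reproduce, and neither depends on this point. No precision or power is stated for depression or anxiety.

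**Precision as planned.** Take 70 evaluable women per arm and express results in units of the score's SD at one visit. The group-by-time model with independent working correlation compares the two arm means at each visit.

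- SE of the difference = √(2/70) = 0.169 SD
- 95% CI half-width = 1.96 × 0.169 = 0.331 SD
- Difference detectable with 80% power = (1.960 + 0.842) × 0.169 = 0.474 SD

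**Precision with a baseline covariate.** If r is the correlation between the T0 score and the score at a visit, adjustment multiplies the variance of the difference by 1 − r² and the SE by √(1 − r²). The equivalent unadjusted size is 70 / (1 − r²). The protocol gives no r, so a range is assumed.

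| Assumed r | √(1 − r²) | SE reduction | CI half-width (SD) | Detectable difference (SD) | Equivalent n per arm | Power for a 0.474 SD effect |
|---|---|---|---|---|---|---|
| none (as planned) | 1 | – | 0.331 | 0.474 | 70 | 80% |
| 0.3 | 0.954 | 4.6% | 0.316 | 0.452 | 77 | 84% |
| 0.5 | 0.866 | 13.4% | 0.287 | 0.410 | 93 | 90% |
| 0.7 | 0.714 | 28.6% | 0.237 | 0.338 | 137 | 97.5% |
| 0.8 | 0.600 | 40.0% | 0.199 | 0.284 | 194 | 99.7% |

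**Where the gain arises.** Collecting a T0 score would not change the result by itself, because the section 3.6 models would not use it. Both the schedule and the model have to change. The gain applies to the treatment effect at a visit and to the treatment main effect. A baseline covariate with one common slope drops out of within-woman changes between visits, so it does little for the interaction test.

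**The case against.** The strongest reply is that nothing here is contradictory or miscalculated. A randomised comparison of post-treatment scores is valid, and these are two of six secondary outcomes with no power claim attached. That stands, and it makes this an efficiency point.

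Three stronger readings are tempting, and the protocol supports none of them.

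- **That no pre-treatment score exists.** The T0 baseline data are not itemised and could include both scales. The outcome list does not settle it, because sleep is measured at T0 yet listed only from T2. What can be said is that no such score is specified.
- **That the outcomes are far less precise.** No correlation is given. Section 3.2 excludes a history of psychiatric disorders, which may narrow the spread between women. The anxiety scale concerns pregnancy, so a score taken before delivery may track later scores less closely. The T8 assessment is a month later and by telephone. A low r is therefore possible, and at r = 0.3 the gain is small.
- **That a chance imbalance at entry would be mistaken for an effect.** With 78 per arm, the SD of such an imbalance is √(2/78) = 0.16 SD. That is the ordinary standard error of a two-group difference. Allocation is 1:1 and concealed (section 3.3), so the confidence interval and P value already allow for it. It is not an added bias.

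It is also fair to say that adjustment would not rescue small effects. For a true difference of 0.3 SD with 70 per arm, power rises from about 43% to 54% (r = 0.5) or 70% (r = 0.7). Nor is the missing covariate peculiar to these two outcomes: the pain and sleep models also leave out the pre-treatment score that those outcomes do have.

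**Conclusion.** The point holds as a modest loss of efficiency. Sections 3.4 and 3.5.2 both begin depression and anxiety at T2, and section 3.6 leaves no place for a baseline score. Followed as written, the plan compares these outcomes on post-treatment scores alone and offers no check of entry balance on them. The comparison remains unbiased.

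The loss is small to moderate up to about r = 0.5 and becomes large only from about r = 0.7. These figures assume 70 evaluable women per arm, one visit at a time, a linear relation between baseline and follow-up, and a correlation that the protocol does not supply. The primary outcome and the sample size are not touched.

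**What to change.** In section 3.4, name the EPDS and PRAQ-R2 among the T0 assessments, or state that the T0 baseline data already include them. In section 3.6, add each T0 score as a covariate in its own GEE model for T2 to T8. T0 comes before the allocation is revealed, so the score cannot be affected by treatment.

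The cost is two 10-item questionnaires, a few minutes at a visit that already takes place, and one extra covariate per model. The added burden on participants the day before surgery is small.
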